# An efficacy and safety study of rivaroxaban for the prevention of deep vein thrombosis in patients with left iliac vein compression treated with stent implantation (PLICTS): study protocol for a prospective randomized controlled trial

**DOI:** 10.1186/s13063-020-04742-z

**Published:** 2020-09-29

**Keywords:** Left iliac vein compression syndrome, Thrombotic, Warfarin, Rivaroxaban, Stent implantation

## Abstract

**Background:**

Balloon dilatation with stent implantation has been proved to be an effective option for left iliac vein compression syndrome (LIVCS), but thrombosis may still occur after the operation. Currently, warfarin is used for anticoagulant therapy, but long-term monitoring is required, while rivaroxaban does not need laboratory monitoring, which can simplify treatment. Therefore, this study aimed to compare the efficacy and safety of rivaroxaban and warfarin in anticoagulation.

**Methods:**

This study is a multicenter, randomized controlled trial. We will recruit 224 patients with thrombotic LIVCS from 9 hospitals. Moreover, these patients will be randomized to either the experimental group (rivaroxaban) or the control group (warfarin plus nadroparin). The primary outcome is stent occlusion rate. Secondary outcomes are quality of life scale survey results, all-cause mortality, anticoagulation-related mortality, and the proportion of participants with stent displacement/fracture, thrombosis, hemorrhage, and other vascular events.

**Discussion:**

This study will provide reliable, evidence-based clinical evidence for the efficacy and safety of rivaroxaban antithrombotic therapy after stent implantation.

**Trial registration:**

ClinicalTrials.gov NCT04067505. Registered on August 26, 2019.

## Background

Left iliac vein compression syndrome (LIVCS) is a disease of iliac vein stenosis/occlusion caused by chronic friction and compression of the left iliac vein by the right common iliac artery and lumbar vertebra, which results in blood flow disorders in lower limbs and pelvic veins. It is also called Cockett syndrome [1] or May-Thurner syndrome [2]. Left iliac vein stenosis or occlusion can cause a deep venous thrombosis, and chronic venous insufficiency of the left lower extremity, manifesting as swelling, pain, varicose veins, skin pigmentation, skin dystrophy, and venous ulceration in severe cases, affect the quality of life and labor capacity. With the growing awareness of this disease and the development of various imaging examinations, the detection rate of LIVCS has gradually increased [3, 4]. The incidence of LIVCS was about 14.8% in patients with uncomplicated venous insufficiency of the left lower extremity [5]. Moreover, 50 to 60% of patients with left iliac vein thrombosis have left iliac vein compression [6]. Recently, left iliac vein balloon dilatation with stent implantation has been used to treat patients with LIVCS and have achieved good results [7, 8].

Interventional treatment of iliac vein stenosis or occlusion can directly cause local trauma and intimal injury, which is a clear inducement of local thrombosis. Therefore, high-intensity anticoagulation therapy is still needed to prevent secondary thrombosis in a stent after left iliac vein balloon dilatation with stent implantation. At present, the postoperative anticoagulation regimen of these patients is early heparin anticoagulant therapy and later warfarin anticoagulant therapy. Warfarin is a standard oral anticoagulant for a long time, with good anticoagulant effect and low price. However, due to the narrow therapeutic window of the drug, patients need to adjust the dosage according to the coagulation function under the guidance of doctors. However, doctors at grass-roots level are not familiar with the use of warfarin, coupled with patients’ lack of awareness of warfarin, resulting in more difficult follow-up management, the uncertain treatment effect of warfarin, and even severe bleeding complications [9]. On the one hand, according to relevant research data, the incidence of warfarin-related bleeding is about 1–2% [9], among which intracranial hemorrhage is about 0.76% per year, which is the most worrying bleeding complication [10]. On the other hand, due to the need for repeated visits, some patients automatically give up treatment, resulting in recurrence or aggravation of thrombosis.

Rivaroxaban is a direct oral anticoagulants (DOACs) that function as a factor Xa inhibitor. It is more safe and can simplify treatment. It is also not easy to interact with food or drugs. Previous studies have shown that rivaroxaban is effective in preventing deep venous thrombosis after orthopedic surgery [11, 12]. Rivaroxaban has also been reported to be safe and effective in anticoagulation therapy for patients with deep venous thrombosis and pulmonary embolism, and laboratory monitoring is not required [13–15], while due to the limitation of indications, DOAC is mainly used for the prevention and treatment of venous thrombosis. Rivaroxaban lacks sufficient clinical data for adjuvant anticoagulation therapy after balloon dilatation with stent implantation. Therefore, we design this study to access the efficacy and safety of rivaroxaban for the prevention of deep vein thrombosis in patients with left iliac vein compression treated with stent implantation.

For the postoperative oral anticoagulation regimen for patients with LIVCS, this study will evaluate the efficacy and safety of rivaroxaban after stent implantation in the left iliac vein through a prospective, randomized controlled trial. Also, this study will provide the basis for LIVCS treatment guidelines and explore the clinical indications of rivaroxaban.

## Methods

### Study design and setting

The study is a prospective, randomized, multicenter, controlled trial that will evaluate the efficacy and safety of rivaroxaban for the prevention of deep vein thrombosis in patients with left iliac vein compression syndrome treated with stent implantation. The ethics committee approved the study at each participating hospital and written informed consent will be obtained from patients before enrolment. Doctors in charge of each center is responsible for this work. The independent adjudication committee blinded to the intervention will adjudicate all events. We will randomly allocate patients to either the experimental group or the control group after enrollment. The study was registered in the website of ClinicalTrials.gov (registration no. NCT04067505). And the study design is described in Fig. 1.

**Fig. 1 Fig1:**
[figure not shown]
The procedure of screening, randomization, and follow-up of patients in the trial

### Sites and patients

Before the start of this study, a total of 9 hospitals participating in the trial fully communicated to determine the clinical diagnosis and treatment procedure of LIVCS according to the existing clinical guidelines or routines. Moreover, the anticoagulation treatment and monitoring program after stent implantation were also formulated. The diagnosis and treatment process, diagnostic criteria, and research protocols were published and unified training at the kick-off meeting.

For this study, we will recruit patients aged 18 to 75 with LIVCS from 9 sites in China. The diagnostic criteria of LIVCS (all need to meet the following three standards) are as follows: (1) definite clinical manifestations of deep venous thrombosis or venous insufficiency of the left lower extremity, such as swelling, pain, heaviness, skin dystrophies, venous ulcers; (2) the visualization of a > 50% reduction in the luminal diameter of the vein according to color Doppler ultrasound (DUS) and computed tomography venography (CTV); (3) the formation of collateral circulation; and (4) a pressure gradient of > 2 mmHg across the stenosis while the patient was in a supine position [5]. According to the clinical diagnosis and treatment process of LIVCS, the participating hospitals will perform left iliac vein color Doppler ultrasound and left iliac vein CTV screening for patients with the above-mentioned symptoms. Patients in accordance with the diagnostic criteria will be diagnosed as LIVCS. Patients with a definite diagnosis of left iliac vein compression syndrome who conform to the following inclusion and exclusion criteria will be included in the study.

The inclusion criteria are as follows: patients with thrombotic LIVCS who underwent left iliac vein stent implantation. Patients with following conditions will be excluded: age < 18 years or age > 75 years; with a history of pelvic surgery, left iliac vein trauma or pelvic radiotherapy; with obvious contraindications for anticoagulation therapy; allergic to iodine contrast agents in the past; with concomitant diseases that need high-intensity anticoagulation; the anticoagulation intensity is higher than that of the patients with iliac vein therapy alone; active bleeding or potential bleeding risk; pregnant or breastfeeding women; with pelvic tumors causing compression of left iliac vein; with chronic venous insufficiency of lower extremities caused by K-T syndrome; with malignant tumors and life expectancy < 1 year; and taking CYP-450 3A4 inhibitors or inducers.

### Randomization and blinding

Blocked randomization was adopted. We will conduct central randomization based on the research electronic data capture (REDCap) system. REDCap system was developed by Paul Harris of Vanderbilt University [16]. A randomization module is put in this system. So, someone who is not involved in this study will generate the allocation sequence by REDCap system, in order to ensure allocation concealment. Then, patients will be randomly assigned to either the experimental group or the control group. It is an open-label study, while assessors will be blinded after assignment to interventions.

### Treatment/protocol of therapy

Inclusive patients will receive left iliac vein stent implantation. Participants in the experimental group will receive rivaroxaban 15 mg twice daily for 3 weeks, then 20 mg oral once daily until 6 months after the operation. Moreover, participants in the control group will receive subcutaneous nadroparin, 1.0 mg per kilogram of body weight twice daily, plus warfarin 3 mg oral once daily for 5 days after the operation, and later warfarin (oral) at individually titrated doses (0.75 mg to 18 mg) to achieve a target international normalized ratio (INR) of 2.0 to 3.0, once-daily until 6 months.

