### Criteria for discontinuing or modifying allocated interventions

The standards for warfarin withdrawal or reduction were described previously [17] (Supplementary Appendix). Patients in the experimental group should stop using rivaroxaban when they have life-threatening bleeding.

Participants should withdraw from this clinical trial when they have active bleeding after anticoagulant administration, diseases that cannot continue anticoagulation, or surgery which need to stop anticoagulation. The detailed definitions for bleeding were described in Supplementary Appendix [18]. We will purchase insurance for all participants to cover study-relate adverse events.

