### Sample size calculation

According to Snyder et al., stent occlusion rate of thrombotic LIVCS was 20.2% [21]. For the noninferiority test of group design, 202 cases recruited in the study are enough under the power of 0.8, two-sided alpha level of 0.05, and the non-inferiority margin of 0.1. We will include 224 samples in the study, taking into account a dropout rate of 10%, 112 in the experimental group, and 112 in the control group.

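### As naturally read, the control regimen stops nadroparin on day 5 with no INR condition, so some controls could be on warfarin alone below the protocol's own floor of 2.0

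*Protocol article*

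**What the plan says.** The control regimen is a single sentence under Treatment/protocol of therapy. It opens with "participants in the control group will receive subcutaneous nadroparin, 1.0 mg per kilogram of body weight twice daily" and continues "plus warfarin 3 mg oral once daily for 5 days after the operation, and later warfarin (oral) at individually titrated doses". The titrated phase is described as "individually titrated doses (0.75 mg to 18 mg) to achieve a target international normalized ratio (INR) of 2.0 to 3.0", and it runs to 6 months.

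Three other places bear on the point:

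- **Background** says that "high-intensity anticoagulation therapy is still needed to prevent secondary thrombosis in a stent" after dilatation and stenting. Of warfarin it says that "due to the narrow therapeutic window of the drug, patients need to adjust the dosage according to the coagulation function".
- **Criteria for discontinuing or modifying allocated interventions** points to the appendix: "The standards for warfarin withdrawal or reduction were described previously". It also refers there for bleeding definitions.
- **Sites and patients** reports that "the anticoagulation treatment and monitoring program after stent implantation were also formulated" among the nine hospitals before the start. The article does not give the content of that program.

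**The concern.** The sentence appears to fix the end of heparin cover by date and the early warfarin dose by number, and neither depends on how far the individual patient is anticoagulated. The INR enters only afterwards, as the aim of titration. A control who has not reached 2.0 by day 5 would then stop nadroparin and continue on warfarin alone, below the range that the protocol itself sets, in the first days after stenting.

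Two things are at stake. One is patient protection in the period for which the Background asks for the most intense anticoagulation. The other is the comparison. The rivaroxaban arm takes fixed doses (15 mg twice daily for 3 weeks, then 20 mg once daily) and has no equivalent hand-over, so a gap of this kind can arise in controls only. In a trial sized for non-inferiority on stent occlusion, a weaker control arm makes the new drug easier to pass.

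**Working it through.** The plan gives no figure on this point, so there is none to reproduce. The check is mainly a reading of the text, with one line of algebra for the direction.

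**1. When does nadroparin stop?** There are two ways to parse the sentence.

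- The 5 days cover both drugs. Nadroparin then stops on day 5. This is the natural reading, because the next phase names warfarin only.
- The 5 days cover only the 3 mg warfarin dose. The sentence then gives no stopping point for nadroparin.

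Neither parsing makes an INR value a condition for stopping nadroparin.

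**2. Does another section supply the condition?** The discontinuation section cites rules for withdrawing or reducing warfarin, which is a different matter from ending nadroparin. Surveillance and follow-up lists visits from 1 month onward. That neither supplies a rule nor shows that no INR is measured before then. Sites and patients mentions a monitoring program whose content is not shown. So the article contains no such condition, and the program may or may not contain one.

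**3. Can a uniform 3 mg be expected to bring every control to 2.0 by day 5?** The inputs are the starting dose of 3 mg and the titrated range of 0.75 to 18 mg, both from the treatment section.

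- Upper limit relative to starting dose: 18 / 3 = 6.
- Width of the range: 18 / 0.75 = 24-fold.

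A protocol that allows up to six times the starting dose to hold the INR at 2.0 to 3.0 expects patients for whom 3 mg is not enough. Those patients are the ones who could still be below 2.0 when nadroparin ends. The range shows that such patients are foreseen; it does not say how many there are.

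**4. Direction of any effect on the primary outcome.** Let f be the share of controls below 2.0 when nadroparin stops, and e the added occlusion risk in those patients.

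- Control rate = 20.2% + f × e, where 20.2% is the rate in Sample size calculation.
- Difference (rivaroxaban minus control) falls by f × e.

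A smaller difference favours non-inferiority. The documents give neither f nor e. As assumptions only:

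| f (assumed) | e (assumed) | f × e | Control rate |
|---|---|---|---|
| 10% | 5 points | 0.5 points | 20.7% |
| 30% | 10 points | 3.0 points | 23.2% |
| 50% | 20 points | 10.0 points | 30.2% |

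If either f or e is zero, nothing changes. The last row assumes that half of all controls are below target and that their occlusion risk roughly doubles (20.2% to 40.2%) because of a gap of unknown length. The table shows the direction and how wide the uncertainty is. It is not an estimate.

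**The case against.** The strongest reply is that a journal article condenses a fuller protocol. Rules for overlapping heparin and warfarin are operational detail of the kind that a jointly agreed monitoring program would hold, and the sites were trained on common procedures. If the program has an INR rule, only a summary sentence is loose. The sentence also never says outright that nadroparin stops on day 5 whatever the INR.

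A second reply is that the Background is not contradicted. Its remark on adjusting the dose explains why warfarin is burdensome to manage. A fixed starting dose followed by titration is compatible with that remark, and also with the Background's account of usual care as early heparin followed by warfarin. A third reply is that nothing in the documents says how quickly the INR rises on 3 mg.

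Much of this stands. The grammar is ambiguous, the program may already hold the rule, and the likely number of patients below target is unknown. What remains is that the article is not silent on the switch: as naturally read, it states one, by date and fixed dose. A site that followed the sentence literally would have no instruction to wait for the INR.

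A reader might go further and infer that the control arm will be under-treated, or that a non-inferiority result would be invalid for this reason. The documents do not support either inference. They contain no INR data, no length of gap and no occlusion risk tied to one, and actual conduct may follow a program that is not shown.

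**Conclusion.** The point holds as a weakness in how the control regimen is specified. On its natural reading the text ends nadroparin on day 5 with no INR condition, while its own dose range implies that some controls will not yet have reached 2.0. Those controls would be on warfarin alone below target when the protocol says that high-intensity anticoagulation is needed. Any such under-treatment falls on controls only and would tend to favour rivaroxaban. Its size cannot be derived from the documents, and no effect at all is possible.

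The conclusion assumes that the 5 days apply to both drugs and that no unseen site rule already governs the switch. If the first assumption fails, the sentence does not say when nadroparin stops, and the same edit is needed. If the second fails, the point reduces to wording. This is a cheap improvement, not a defect that undermines the trial.

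**What to change.** Reword the control regimen in Treatment/protocol of therapy along these lines:

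*Nadroparin is continued for at least 5 days and until the INR is at least 2.0. Warfarin is started at 3 mg once daily and titrated to INR.*

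The value 2.0 is the lower limit of the protocol's own target. If the monitoring program mentioned under Sites and patients already contains this rule, align the sentence to it; conduct then does not change.

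The cost is one or two sentences and a notice to sites. The downside is that some controls would have injections for longer and somewhat more bleeding exposure while both drugs overlap, which could add control events to the hemorrhage secondary outcome. The sample size is unaffected.

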### Criteria for discontinuing or modifying allocated interventions

The standards for warfarin withdrawal or reduction were described previously [17] (Supplementary Appendix). Patients in the experimental group should stop using rivaroxaban when they have life-threatening bleeding.

Participants should withdraw from this clinical trial when they have active bleeding after anticoagulant administration, diseases that cannot continue anticoagulation, or surgery which need to stop anticoagulation. The detailed definitions for bleeding were described in Supplementary Appendix [18]. We will purchase insurance for all participants to cover study-relate adverse events.

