### Surveillance and follow-up

All participating hospitals use the same electronic case report form (eCRF) available at REDCap system to collect data of patients. All centers participating in the trial, ethics committee, and statisticians will have access to the system. Patients’ identity information is encrypted to prevent leakage. An independent data monitoring committee is responsible for summarizing and checking the data of each center. Moreover, if they have any questions, they can contact the co-investigators of each center to review or revise. Both the rivaroxaban group and the control group will be followed at 1, 3, 6, 12, 18, and 24 months after the operation. Once bleeding, thromboembolism, or other adverse events occur, patients need to report to the hospital immediately. The schedule of enrolment, interventions, and assessments is shown in Fig. 2.

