### Statistical analysis

We will perform statistical analysis on an intention-to-treat (ITT) basis. All data will be reported as mean ± standard deviation or numerical value (percentage). Non-normal distribution data will be presented as median (quartile interval, IQR). The chi-square test will be used to compare the categorical variables between the two groups. Continuous variables will be compared using sample *t* test for normally distributed data and Mann-Whitney *U* test for continuous variables of abnormal distribution. A non-corrected chi-square test will first compare the outcome variables of binary classification, and then the Cox proportional hazards model will be established to correct other confounding factors. The survival differences of the patients between the two groups will be compared using Log-Rank, and Kaplan-Meier survival curves will describe the results. Statistical analysis will be performed by using GraphPad Prism, and software R. *P* < 0.05 will be considered statistically significant.

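### Patients who bleed, or who must stop anticoagulation, are withdrawn from the trial rather than only from study drug, so their later outcomes would be lost

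*Protocol article*

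**What the plan says.** The section Criteria for discontinuing or modifying allocated interventions holds two kinds of instruction. The first concerns the drug. Standards for reducing or stopping warfarin are referred to a supplementary appendix, and for the other arm: "Patients in the experimental group should stop using rivaroxaban when they have life-threatening bleeding". The second concerns the trial: "Participants should withdraw from this clinical trial when they have active bleeding after anticoagulant administration", with the same consequence for diseases that preclude anticoagulation and for surgery that requires it to be stopped.

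Three other sections bear on this:

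- Treatment/protocol of therapy: rivaroxaban is given at a higher dose for three weeks, "then 20 mg oral once daily until 6 months after the operation". Warfarin also runs to 6 months.
- Surveillance and follow-up: "Both the rivaroxaban group and the control group will be followed at 1, 3, 6, 12, 18, and 24 months after the operation". On events: "Once bleeding, thromboembolism, or other adverse events occur, patients need to report to the hospital immediately". Nothing is said about patients who have been withdrawn.
- Statistical analysis: "We will perform statistical analysis on an intention-to-treat (ITT) basis". The methods include a chi-square test, a Cox model and a log-rank test, and "Kaplan-Meier survival curves will describe the results".

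**The concern.** All three triggers arise after randomisation, and bleeding is plausibly affected by which anticoagulant the patient receives. A patient who meets one of them will usually stop anticoagulation. The article's Background says that intensive anticoagulation is needed after stenting to prevent thrombosis in the stent. On its own account, then, the patients removed are those whose later risk of occlusion has gone up.

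If they leave the trial, later stent occlusion (the primary outcome), thrombosis and death are not collected for them. Kaplan-Meier, log-rank and Cox methods assume that censoring is unrelated to risk. That assumption fails when the reason for censoring is a bleed or a forced stop of anticoagulation. In a non-inferiority trial, events lost from the worse arm can make a drug that is truly inferior look acceptable.

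**Working it through.** **1. Reading the sections together.** The drug rule speaks of ceasing rivaroxaban. The next paragraph speaks of leaving the clinical trial and has broader triggers: active bleeding of unstated severity, disease, and surgery. The follow-up section plans 24 months for both arms but has no sentence keeping withdrawn patients in it. The analysis section promises intention-to-treat. The withdrawal rule does not contradict that promise, because a withdrawn patient can still be counted in the assigned arm. What it removes is the outcome to be counted.

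**2. Visits lost.** Scheduled visits are at months 1, 3, 6, 12, 18 and 24. A patient withdrawn during the 6-month treatment period, before the month-6 visit, misses at least months 6, 12, 18 and 24: four of six. The bleed that triggers withdrawal is still recorded, since patients must report bleeding at once.

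**3. The dropout allowance.** The sample size is raised from 202 to 224, "taking into account a dropout rate of 10" per cent: 202 / 0.90 = 224.4. This restores numbers. It does nothing about which patients are missing.

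**4. Size of the bias.** The article gives no withdrawal rates, so this is an illustration on assumed values.

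Inputs from Sample size calculation: control occlusion rate 20.2%, margin 10 points, 112 per arm. Assumptions:

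- Rivaroxaban is truly worse by exactly the margin: pR = 0.302 against pC = 0.202.
- A share w of each arm is withdrawn (wR, wC).
- Withdrawn patients have twice their arm's overall risk, and all their events are lost. Losing every event is the upper bound for that risk.

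Two ways of handling the withdrawn patients bracket the result:

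- Scored as event-free: p' = p(1 − 2w), n' = 112.
- Excluded: p' = p(1 − 2w)/(1 − w), n' = 112(1 − w).

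Then d = p'R − p'C, SE is the unpooled standard error, and P(non-inferiority declared) = Φ((0.10 − d)/SE − 1.96).

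Example, 10% rivaroxaban and 5% control, event-free: p'R = 0.302 × 0.80 = 0.2416; p'C = 0.202 × 0.90 = 0.1818; d = 0.0598; SE = 0.0544; P = Φ(0.0402/0.0544 − 1.96) = 0.111.

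| Withdrawn, rivaroxaban / control | Event-free: d, SE, P | Excluded: d, SE, P |
|---|---|---|
| 0 / 0 | 0.1000, 0.0576, 0.025 | same |
| 1% / 2% | 0.1020, 0.0571, 0.023 | 0.1011, 0.0578, 0.024 |
| 2% / 2% | 0.0960, 0.0569, 0.029 | 0.0980, 0.0578, 0.027 |
| 2% / 1% | 0.0920, 0.0571, 0.034 | 0.0959, 0.0578, 0.029 |
| 5% / 10% | 0.1102, 0.0546, 0.016 | 0.1065, 0.0581, 0.019 |
| 5% / 5% | 0.0900, 0.0556, 0.038 | 0.0947, 0.0581, 0.031 |
| 10% / 5% | 0.0598, 0.0544, 0.111 | 0.0771, 0.0583, 0.059 |

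**5. Where the direction changes.** With event-free scoring there is no bias when wR × pR = wC × pC, that is wC/wR = 0.302/0.202 = 1.50. With exclusion the ratio runs from 1.49 (wR = 1%) to 1.42 (wR = 10%). Below that ratio, including equal withdrawal, the error is anti-conservative, because more events are lost from the worse arm.

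**6. When there is no bias.** If withdrawn patients carry only their arm's average risk and are excluded, d = 0.1000 and P = 0.025 in every row.

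**The case against.** The strongest reply is that the sentence stands under a heading about interventions. Follow-up to 24 months is stated without exception, study drug stops at 6 months so off-drug follow-up is already the design, and the analysis is intention-to-treat. The authors may simply have meant withdrawal from study drug. The appendix with the bleeding definitions, the follow-up figures and the full protocol are not shown, so the breadth of active bleeding cannot be judged. This bears on intent, and it is why the point is put as what follows from a literal reading. It does not remove the problem. The article uses drug-stopping language for one rule and trial-leaving language for the next, nine hospitals must apply the sentence as written, and no analysis plan can recover visits that were not made.

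The second reply is about size. The only bleeding rate in the article is 1% to 2% for warfarin, in the Background, and at such rates the error stays close to nominal. The article also expects rivaroxaban to be the safer drug, which would push control withdrawals up and make the error neutral or conservative. This stands as a limit on size, although disease and surgery add to withdrawals from bleeding.

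Third, the illustration uses a fixed-time risk difference, not a censoring model, and discards events before withdrawal that a time-to-event analysis would keep. That is also fair. The figures indicate order of magnitude and are not an estimate of the censoring bias in the Cox or log-rank analysis.

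**Conclusion.** The concern holds. As written, the rule takes patients out of the trial for treatment-related, post-randomisation reasons, and nothing in the article keeps them in follow-up. The direction of bias cannot be determined from the article.

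Under the stated assumptions (true difference at the margin, doubled risk, all events lost), bias is at most 0.8 points against the 10-point margin when 1% to 2% of each arm withdraws. It reaches about 2.3 to 4.0 points with 10% withdrawn on rivaroxaban and 5% on control, and it turns conservative once control withdrawals are about 1.5 times those on rivaroxaban. The effect is probably modest if withdrawal is rare. It should still be fixed before recruitment, because the lost data cannot be recovered and the correction is cheap. Confidence is medium, since the authors may have intended withdrawal from drug only.

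**What to change.** Reword the withdrawal sentence so that active bleeding, a disease precluding anticoagulation, or surgery requiring its interruption leads to discontinuation of study drug only. Add that all scheduled visits, imaging and event follow-up continue to 24 months unless the patient withdraws consent, and that every randomised patient is analysed in the assigned arm.

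The cost is a change to the protocol and consent wording, plus keeping these patients in visits that already exist: study drug ends at 6 months for everyone, and visits run to 24 months. According to Trial status, recruitment had not begun, so the change could be made before any patient is affected.
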